# Efficacy of Yijinjing combined with Tuina for patients with non-specific chronic neck pain: study protocol for a randomized controlled trial

**DOI:** 10.1186/s13063-021-05557-2

**Published:** 2021-09-03

**Keywords:** Non-specific chronic neck pain, Efficacy, Randomized controlled trial, Tuina, Yijinjing

## Abstract

**Background:**

Non-specific chronic neck pain (NCNP) is a common musculoskeletal disorder which has caused a huge economic burden due to its expensive health costs and high re-occurrence rate. Yijinjing and Tuina are widely used for non-specific chronic neck pain in China. But there is little scientific evidence to evaluate their efficacy for NCNP. The aim of this research is to compare the efficacy of Yijinjng combined with Tuina versus Tuina for patients with NCNP.

**Methods/design:**

A randomized controlled trial in which 102 patients with non-specific chronic neck pain will be recruited and randomly allocated to either the Tuina group or the Yijinjng combined with Tuina group in a 1:1 ratio. The interventions for both groups will be carried out three times a week for 8 weeks. The patients in the two groups will receive follow-up 1 month after the intervention. The primary outcome will be the changes in the visual analog scale (VAS). Secondary outcomes will be measured by the Neck Disability Index (NDI), Self-Rating Anxiety Scale (SAS), and Tissue Hardness and Active Range of Motion (AROM). The data will be analyzed at the baseline, 4 weeks during the intervention, at the end of the intervention, and 1 month after the intervention. The significance level sets as 5%. The safety of interventions will be evaluated after each treatment session.

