### Interventions

The Tuina protocol used in this trial is the same as those used in our previous studies [38, 39]. It includes soft tissue manipulation and spinal manipulation, such as rolling, pressing, and tapping. Yijinjng for NCNP patients was designed on the basis of the textbook which has been used for teaching students in the universities of TCM [40, 41].

Participants in the Tuina group or the Yijinjng combined with Tuina group will receive Tuina treatment 3 times a week for 8 weeks. The treatment room will be controlled at 23–25° to ensure that the participants feel comfortable. The participants will be asked to rest for 15 min before Tuina treatment. They will be advised to lie in the prone position during the treatment. The intensity level of Tuina is based on physical examination and the therapist’s clinical experience, as well as after careful communication with each study participant. Tuina treatment will last for 25 min.

The participants who are in the Yijinjng combined with Tuina group will practice Yijinjing 3 times a week for 8 weeks. The patients will be assembled once a week for practicing Yijinjing together. The Yijinjing teacher will teach them how to practice Yijinjing. The teacher will also correct the wrong movement of patients. The patients will practice Yijnjing another two times per week at home. A digital video disk about the movements of Yijinjing in this trial will be provided to the participants. They can review the movements at home easily. The participants are asked to film themselves and sent it to the teacher by email or WeChat. The teacher will examine the participants’ video carefully and give the patients some advice about practicing Yijinjing. Yijinjing treatment will last for 30 min.

VAS, NDI, SAS, soft tissue hardness, and AROM will be assessed at the baseline and 4, 8, and 12 weeks.

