### Safety evaluation

The safety of patients will be monitored in every visit. Two attending physicians and two responsible spine care specialists will be responsible for the collaboration and guidance of clinicians during each clinical trial and implementation. The two chief spinal surgeons constitute the endpoints Adjudication Committee, which is responsible for the overall supervision of the clinical trials. The AES in trial are changes in pain, syncope, vertigo, and disability. For any AES, no matter if it is or not caused by intervention, the treatment will be stopped immediately. The patient should take any medical aids to alleviate symptoms. The adverse events should be reported to the relevant responsible unit and the ethics committee in time. If the adverse events are confirmed to be related to the study, the regional Ethics Review Committee of Yueyang Integrated Traditional Chinese and Western Medicine Hospital affiliated to Shanghai University of Traditional Chinese Medicine has the right to suspend the study. If an adverse event occurs during the clinical trial, medical experts will be engaged to assess and investigate the actual cause, and medical and financial compensation will be made to participants.

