### Statistical analysis

All statistical analyses will be performed with the SPSS software (SPSS, version 24.0, SPSS Inc., Chicago, IL, USA) by statisticians who are independent of the research team and blinded to the group allocation. Data analysis will be based on the intention-to-treat (ITT) principles. The statistical significance was accepted for values of *p* < 0.05. Participants who fail to complete the study will be treated as having no change from baseline at all times. Descriptive statistics will be used to compare demographic and baseline information and evaluate the credibility of the groups. The normality of data will be tested by the Kolmogorov-Smirnov test. Parametric statistics (Tukey test) or non-parametric statistics (Wilcoxon rank sum test) will be used for the within- and between-group according to the results of homogeneity and normality analysis. If the data does not conform to a normal distribution, a covariance analysis will be used. The efficacy will be measured at four time points. A repeated measures analysis of variance will be conducted to analyze dependent variables (from baseline and follow-up). The Bonferroni and Dunn tests will be used for multiple comparisons. The intra-group comparison (comparison between baseline and follow-up) will be tested by a two-sided paired *t* test. The difference of categorical variables (VAS, NDI, SAS, PPT, AROM) and adverse effects between the groups will be analyzed by using The chi-square test or Fisher’s exact test. All numerical data will be presented as the mean ± SD, and categorical variables will be described with percentages (%). If it is necessary, post hoc analyses will be performed. The confidence interval will be established at 95% and the significance level at 0.05.

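### The session-based and visit-based safety rules differ only in the combined arm, so the adverse-event comparison has no common ascertainment schedule and the 16 home sessions have no stated check

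*Protocol article*

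**What the plan says.** The protocol article gives two rules for when safety is assessed. The abstract (Methods/design) ties it to sessions: "The safety of interventions will be evaluated after each treatment session". The Safety evaluation section ties it to attendance: "The safety of patients will be monitored in every visit".

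The Interventions section sets the contacts. Patients in either arm "will receive Tuina treatment 3 times a week for 8 weeks". Those in the combined arm also "will practice Yijinjing 3 times a week for 8 weeks". One of the three weekly Yijinjing sessions is a class with the teacher: "The patients will be assembled once a week for practicing Yijinjing together". The rest are not attended: "The patients will practice Yijnjing another two times per week at home". Patients send the teacher a film of their practice, and the stated purpose is advice on technique.

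The Statistical analysis section plans a test between arms: "adverse effects between the groups will be analyzed by using The chi-square test", with Fisher's exact test as the alternative. The Safety evaluation section also stops treatment at any adverse event, whatever its cause.

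**The concern.** A comparison of adverse-event proportions is fair only if both arms are asked about events in the same way and equally often. Here the stated moments of assessment follow contacts, and contacts differ by design. If classes count as separate visits, the combined arm has more occasions on which a minor complaint can be noted, and its proportion can rise with no difference in true risk. If only attended occasions count, two thirds of the added treatment (16 of 24 Yijinjing sessions) takes place with no assessment attached, and harm from it may be missed or reported late.

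Either would weaken the safety statement about the component under test. The article's Introduction itself says that adverse event reports are needed for Yijinjing.

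**Working it through.** **1. Session counts (Interventions section).**
- Tuina, both arms: 3 × 8 = 24.
- Yijinjing, combined arm only: 3 × 8 = 24, made up of 1 × 8 = 8 classes and 2 × 8 = 16 home sessions.
- Total sessions: 24 in the Tuina arm and 24 + 24 = 48 in the combined arm.

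**2. Contacts at which safety would be assessed.** The article states no total, so each rule is applied in turn. The outcome assessments at weeks 0, 4, 8 and 12 are the same in both arms and are left out.
- Visit rule (Safety evaluation): 24 in the Tuina arm. In the combined arm, 24 if each class falls on a Tuina day, and at most 24 + 8 = 32 if none does. The home sessions are not visits.
- Session rule (abstract), read literally: 24 against 48. This needs an assessment after each home session, and no section describes one.

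**3. Arm size.** The plan's figure reproduces: 2 × (1.96 + 0.84)² × 1.3² / 0.8² = 41.4, rounded up to 42, and 42 × 1.2 = 50.4, rounded up to 51 per arm.

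**4. Size of an ascertainment effect (illustration).** The article gives no adverse-event rate. Assume a chance q of a newly recorded event at each contact, equal in both arms and independent between contacts. The share of patients with at least one event after k contacts is P(k) = 1 − (1 − q)^k. For q = 0.01, P(24) = 1 − 0.99^24 = 0.214. Rejection rates for Fisher's test (two-sided, 0.05) come from exact enumeration at 51 per arm.

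| q | P(24) | P(32) | P(48) | Fisher 24 v 24 | Fisher 32 v 24 | Fisher 48 v 24 |
|---|---|---|---|---|---|---|
| 0.5% | 11.3% | 14.8% | 21.4% | 2.0% | 4.1% | 19.5% |
| 1% | 21.4% | 27.5% | 38.3% | 3.0% | 7.5% | 38.7% |
| 2% | 38.4% | 47.6% | 62.1% | 3.3% | 12.2% | 62.8% |

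The chi-square test without continuity correction gives 4.9%, 5.0% and 5.3% at 24 v 24, and 7.8%, 11.1% and 16.9% at 32 v 24. The last column of the table is shown only to mark what the literal session reading would imply.

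**5. The opposite direction.** Under-recording of events from the 16 home sessions cannot be quantified. It depends on how many such events would go unmentioned at the next Tuina visit, and the article says nothing on that.

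**The case against.** A reader might infer that the combined arm is assessed 48 times against 24, with a false-positive rate of 20% to 63%. The documents do not support that. The count of 48 is a count of sessions. Just before the safety sentence, the abstract describes one thrice-weekly schedule for both arms: "The interventions for both groups will be carried out three times a week for 8 weeks". The section devoted to safety speaks of visits, and the film review concerns technique.

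The model in the table also favours a large effect. It treats every extra contact as a fresh chance of a new event. In practice both arms are seen at the same 24 Tuina visits over the same 8 weeks, so an event between visits can be reported at the next one in either arm. An extra contact adds only what would otherwise go unreported. Events caused by Yijinjing itself are a true effect of the add-on, and a test that detects them is not falsely positive. All of this stands, and it makes even the 32 v 24 column closer to an upper bound.

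It can also be said that the wording of adverse-event questions belongs to the case report form, which is not shown. That is true of the wording. It does not dispose of two published rules that diverge in one arm. The Data collection section lists adverse events among the items on the form but does not say when they are asked about or whether home practice is covered. Pick-up at the next Tuina visit is plausible, but no section says that those visits ask about the interval since the last one.

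**Conclusion.** The point holds in a limited form. The two safety rules need to be reconciled, because they differ exactly where the arms differ. As written, the adverse-event test rests on 24 to 32 contacts against 24, with no stated assessment of the 16 home sessions. The first feature could inflate the combined arm's event proportion and the second could deflate it, so the net direction is not determined.

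The first effect is modest. Fisher rejection is about 4% to 12%, against 2% to 3% with equal contacts, for assumed per-contact rates of 0.5% to 2%. It is absent if classes fall on Tuina days. These figures rest on assumed rates, on equal and independent risk per contact, and on 51 patients per arm.

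A reader might also infer that unequal recording spreads to the VAS result, since any adverse event stops treatment and non-completers are analysed as unchanged from baseline. The documents do not carry that step. The direction of unequal recording is open. The Dropout criteria name adverse reactions that make a patient quit and removal for serious events, and do not say that every patient whose treatment is stopped becomes a non-completer. Adverse effects are not among the primary or secondary outcomes, so this is a weakness of the safety comparison and not of the efficacy analysis.

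**What to change.** - Reconcile the abstract and the Safety evaluation section into one rule, and state whether home practice and classes are covered.
- Make the 24 Tuina visits, which both arms share, the common ascertainment schedule. At each, put the same question in both arms about all events since the last visit, worded to cover home and class practice. With three visits a week the recall period averages 7 / 3 = 2.3 days.
- Keep every event that is serious or stops treatment in the between-arm comparison, wherever it was first noted. Under the article's rule that any event stops treatment, a patient stopped after an event in class may have no later Tuina visit at which it would be counted. Dropping such events would bias the comparison in favour of the combined arm.
- Record the source of each report (Tuina visit, class, film or other), and add a sensitivity analysis without events noted only in classes or films.

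The cost is one short question on the case report form, with a source field, at visits that already take place. Recruitment was already under way according to Trial status, so the change should start in both arms on the same date.

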**Discussion:**

The purpose of this trial is to determine whether Yijinjing combined with Tuina is not inferior to Tuina for patients with NCNP. This study will provide clinicians and stakeholders much-needed knowledge for a complementary and alternative therapy for patients with non-specific chronic neck pain.

**Trial registration:**

ChiCTR registry (ChiCTR) 2000036805. Registered on August 25, 2020

## Introduction

Non-specific chronic neck pain (NCNP) is a serious health and public problem worldwide. Neck pain appears between the occipital condyle and C7 in the neck region [1]. Neck pain can be divided into specific neck pain and non-specific neck pain. Non-specific neck pain is also known as mechanical neck pain which is defined as simple neck pain without specific pathological changes and neurological impairments; it can be diagnosed as non-specific chronic neck pain if the symptoms persist more than 3 months [2]. Two-thirds of the adult population suffer from non-specific chronic neck pain [3]. According to the research, women are more likely to be affected than men [4]. The annual incidence of NCNP is increasing because of sedentary lifestyle and working conditions [5, 6]. Patients’ quality of life and efficiency of work decrease due to chronic pain, and high treatment expenses also cause a huge burden to society [7].

The mechanism of NCNP is still not clear. The researchers explained the mechanism from different aspects, such as the mechanical factors, EMG, and ROM. Altered muscle cross-sectional area, thickness, size, and activity of deep neck muscles have been mentioned repeatedly in the previous [8–10]. Rahnama et al. [11] showed the change of altered EMG activity and the atrophy of deep neck extensor in patients with NCNP which is thought to be the recurrence of NCNP. Barnsley et al. [12] demonstrated that limited ROM aggravates the tightness of the muscles surrounding the neck and joint adhesion which also leads to a decrease in bio-mechanical function of the neck, and this condition causes non-specific chronic neck pain. In addition, much attention has been paid to the scapular region. Dyskinesia of the scapula and misalignment of the scapula always follow with NCNP [13, 14]. In addition, according to the “Bio-Psycho-social” framework, repetitive and sedentary working conditions and postural abnormalities also contribute to NCNP [15]. Anxiety and depression are also vital psycho-social factor which is thought to be associated with the existence of higher levels of pain in musculoskeletal pain conditions [16].

For most NCNP patients, first-line medication options always include analgesics like acetaminophen or non-steroidal anti-inflammatory drugs (NSAIDs), but the effects of these drugs vary from person to person and they often do harm to the digestive, blood, urinary, and other systems because of the long-term use [17–19]. So, various complementary treatments have become more and more popular. Exercise therapy, ultrasound, acupuncture, electrical nerve stimulation, and manual therapy have also been used widely in treating NCNP [20]. However, poor standardization of experiments, small sample size, low-quality control, and insufficient objective index caused controversy about their efficacy.

Tuina therapy is also called Chinese massage [21]. Tuina has also been proved to be a feasible way to treat neck pain and has been widely used in China [22]. As an important part of Chinese traditional medicine, Tuina is a manual therapy with anatomical and physiological principles, putting emphasis on meridians and acupoints [23]. Tuina therapy mainly includes two parts: soft tissue manipulation and spinal manipulation. Soft tissue manipulation techniques include stroking, kneading, and drumming, which are also found in some Western massage techniques, and spinal manipulation also combined with high-velocity low-amplitude thrust manipulation techniques [23]. Two systematic reviews had shown that Tuina therapy can reduce pain and muscle tension for patients with non-specific neck pain [24, 25]. Tuina therapy acts on soft tissue and connective tissue that may lead to local biochemical changes that regulate local blood circulation, improve muscle flexibility, enhance lymph movement, and loosen connective tissue adhesion, which may alternately improve local injury and inflammation of the reuptake mediator [26]. Chinese traditional exercise is also a kind of exercise therapy which puts attention on the coordination of posture, meditation, and breathing [27]. Exercise therapy has been proved to be good for non-specific chronic neck pain [28]. Yijinjing is an ancient Chinese traditional exercise which has been widely practiced for keeping fit and treating diseases. Yi means change, Jin refers to muscles and sinews, and Jing means methods, so Yijinjing means a series of exercises to change the muscle and sinews literally. Yijinjing is a low-intensity, non-competitive, and non-impact exercise. TCM doctors often apply Yijinjing as a complementary therapy to NCNP. Yijinjing can reduce neck pain and disability, as well as reduce stress, anxiety, and depression by unique movements [29–31]. Based on previous researches, people can improve sub-health, reduce pain, and promote immune cell by practicing Yijinjing regularly [32, 33]. However, to confirm these findings, more studies with larger sample sizes, standardized trials, and adverse event reports are needed.

Studies have shown that a single treatment plan is not effective, so the combination therapy has received more attention and is recommended by related scholars [34, 35]. There is quite a little evidence for the efficacy of Tuina on non-specific chronic neck pain, especially when combined with Yijinjing. We hypothesize that Tuina and Yijinjing have beneficial effects on non-specific chronic neck pain because that is a case with subacute and long-lasting neck pain [36]. We want to further explore whether Tuina combined with Yijinjing exercises can play a better role in pain, disability, and negative emotions. Thus, we designed a randomized controlled trial (RCT) to prove our hypothesis. This trial will provide a solid clinical foundation for the efficacy of Yijinjng combined with Tuina. It will be served as a prospective experiment as well.

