## Methods/design

### Study design

This present study is a single-center, randomized, and analyst-blinded controlled trial with two arms: Tuina group (control) and Yijinjng combined with Tuina group (intervention). The study protocol has been approved by the Regional Ethics Review Committee of Yueyang Hospital of Integrated Traditional Chinese and Western Medicine affiliated with Shanghai University of Traditional Chinese Medicine (project number: 2020-018). A total of 102 eligible NCNP patients will be recruited and assigned in a 1:1 ratio randomly. Written informed consent will be provided by all patients. Independent researchers who are blinded to the patient assignment will collect and analyze the outcome assessment and related data. The study design is illustrated in the flow chart in Fig. 1. The main treatment center will be the Shanghai University of Traditional Chinese Medicine.

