The present trial is a comparative efficacy of Tuina (control) and Yijinjing combined with Tuina (intervention) for the physical and mental symptoms of NCNP patients. We want to explore whether Yijinjing combined with Tuina is better than Tuina. We will evaluate three aspects of neck pain: pain, physical function, and mental function. we will use validated scales and questionnaires and some measuring instruments to assess the clinical outcomes.

Pain is the most important symptom of neck pain, so visual analog scale (visual analog scale) will be used as the primary outcome. It can evaluate the intensity of neck pain. One of the secondary outcomes is NDI, which can evaluate the limitation of daily life because of NCNP. Cervical active range of motion (AROM) which can evaluate the neck active range of motion is measured by using an easy equipment. SAS can evaluate the anxiety level of patients. Tissue hardness will be measured by a tissue hardness meter and expressed in numbers.

To the best of our knowledge, no study has proved the efficacy of Yijinjing combined with Tuina for patients with NCNP.

High-quality clinical data will be collected because of the rigorous experimental design. The efficacy of this specific intervention protocol for treating NCNP will be evaluated by these data. We hope that this study will provide a solid foundation for the treatment of NCNP, as well as Tuina and Yijinjing research.

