### Strengths and limitation of the study

The strength of this trail includes the randomized study design, the pre-defined sample size, and the application of Yijinjing which is designed by an experienced expert. Secondly, the use of standardized measurement instruments will become very important inclusions for the study. Finally, many resistance trainings are limited to equipment-based ones in rehabilitation organizations or hospitals. They cost high and fail to combined positive and passive movement. As a kind of traditional Chinese exercise, it is easy for people to master in a short time. Moreover, Yijinjing does not require expensive equipment. It can not only strengthen the bones and sinews, but also nourish organs. It will make a positive effect on physiological structures and pathological conditions.

There are several limitations to this study. The first is the blinding of the therapist and patients. The nature of the interventions makes it impossible to blind them during the study. Secondly, self-reported results, such as the VAS and SAS, also have limitations because they may be affected by the placebo effect and expected results. Finally, there is in fact no control group. We use Tuina therapy as a control which is considered experimental.

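### Within-group change is a stated objective and is tested against baseline, but with Tuina in both arms the trial can show only what Yijinjing adds to Tuina

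*Protocol article*

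**What the plan says.** Three consecutive sentences of the Introduction matter. The first is not comparative: "We hypothesize that Tuina and Yijinjing have beneficial effects on non-specific chronic neck pain". The second is comparative: "We want to further explore whether Tuina combined with Yijinjing exercises can play a better role in pain, disability, and negative emotions". The third reads "Thus, we designed a randomized controlled trial (RCT) to prove our hypothesis". The Introduction then promises "This trial will provide a solid clinical foundation for the efficacy of Yijinjng combined with Tuina", and the Discussion adds "The efficacy of this specific intervention protocol for treating NCNP will be evaluated by these data".

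Study design names two arms, Tuina as control and Tuina plus Yijinjing as intervention. The section on the combined arm states that its Tuina steps match those of the control arm. Under Interventions, Yijinjing comes with a weekly taught class, home practice and teacher feedback on participants' videos.

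The specific primary objective (VAS) and the specific secondary objectives each cover change both within and between the groups. In Statistical analysis, "The intra-group comparison (comparison between baseline and follow-up) will be tested by a two-sided paired" t test. The limitations paragraph concedes: "Finally, there is in fact no control group. We use Tuina therapy as a control which is considered experimental".

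**The concern.** Read on its own, the hypothesis sentence asks whether Tuina and Yijinjing work. Answering that for Tuina, or for the combination as a whole, needs a comparison with patients who do not receive Tuina, and the trial has none. The only planned analyses that could seem to answer it are the within-group tests. Such a test measures everything that changes between baseline and follow-up: any treatment effect, the natural course of the pain, expectation in patients who know their treatment (Blinding), and regression to the mean, since entry requires VAS of at least 3 on the primary outcome itself (Inclusion criteria).

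The case to guard against is one where both arms improve significantly from baseline but do not differ from each other. Nothing in the article bars a reading that both treatments have then been shown to work, and the wording of the hypothesis invites it.

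**Working it through.** **1. What the randomised contrast identifies.** Write the expected VAS change as N + T in the Tuina arm and N + T + Y in the combined arm. N is all non-specific change, T the effect of Tuina, and Y what Yijinjing adds on top of Tuina, including its class and feedback. The between-arm difference is (N + T + Y) − (N + T) = Y. The within-arm changes estimate N + T and N + T + Y, and no arm estimates N, so T and T + Y cannot be recovered.

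**2. What the sample size addresses.** Inputs from Sample size calculation: means 5.5 and 4.7, SD 1.3, Δ = 0, z-values 1.96 and 0.84. Then n = 2 × (1.96 + 0.84)² × 1.3² / 0.8² = 2 × 7.84 × 1.69 / 0.64 = 41.4, rounded up to 42 per group. The stated 51 follows from 42 × 1.2 = 50.4. The plan's figures reproduce, and they concern Y only.

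**3. How often a within-arm test is significant when treatment does nothing.** The document gives neither an untreated change nor an SD of change, so both are assumed: a non-specific fall c of 0.3, 0.5 or 0.8 cm and an SD of change s of 1.3 or 1.6. With n = 42, the paired t test has noncentrality c / (s/√42), 41 degrees of freedom and critical value 2.02. The nominal rate in the direction of improvement is 2.5%.

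| Assumed fall c | s = 1.3: noncentrality, rate | s = 1.6: noncentrality, rate |
|---|---|---|
| 0.3 cm | 1.50, 31% | 1.22, 22% |
| 0.5 cm | 2.49, 68% | 2.03, 51% |
| 0.8 cm | 3.99, 97% | 3.24, 89% |

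The plan scores non-completers as unchanged. Adding 9 such patients to the 42 multiplies the noncentrality by about √(s² / (s² + (9/51)c²)). This is 0.97 at its lowest in the table (c = 0.8, s = 1.3), so the pattern stands.

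**4. Regression to the mean alone.** Take a normal source population with mean m, SD s and baseline-to-follow-up correlation r, admitted at VAS ≥ 3. With a = (3 − m)/s and λ = φ(a)/(1 − Φ(a)), the expected spurious fall is (1 − r)·s·λ. The SD of change is √[(1 − r)²s²(1 − λ(λ − a)) + s²(1 − r²)]. The only VAS figures in the document are post-treatment (means 4.7 and 5.5, SDs 1.1 and 1.3). They stand in here for the source population, with r assumed between 0.5 and 0.8.

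| m, s, r | Spurious fall | Rate, n = 42 |
|---|---|---|
| 5.5, 1.1, 0.8 | 0.01 cm | 3% |
| 5.5, 1.3, 0.5 | 0.04 cm | 4% |
| 4.7, 1.1, 0.8 | 0.03 cm | 4% |
| 4.7, 1.3, 0.5 | 0.12 cm | 9% |

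A lower and wider source population (m = 4, s = 2, r = 0.5) would give 0.51 cm and 41%, but nothing in the document supports those values. On the protocol's own figures the entry threshold is a small contributor. Larger error rates would have to come from natural course or expectation.

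**The case against.** The strongest reply is that the trial already asks the right question. The Abstract compares the combination with Tuina. The sample size hypotheses are set on the between-arm VAS difference. The Discussion gives the aim as superiority of the combination over Tuina. In the Introduction, the comparative sentence stands directly before the one announcing the trial. An add-on design is legitimate, the absence of an untreated group is disclosed, and the plan includes between-group tests and a repeated-measures analysis alongside the paired tests. The Introduction also cites two systematic reviews in support of Tuina, so its benefit could be taken as background.

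Most of this stands. A reader might infer that the trial has no valid question, or that the sponsor intends to declare efficacy from within-arm significance. The documents support neither: the between-arm contrast is sound, and no section says how a significant within-group test will be interpreted. The promise of efficacy for the combination also comes from a separate sentence, not from the hypothesis itself.

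The reply does not remove the within-group objectives or their tests, which are stated plan. The limitation is conceded, but the hypothesis and efficacy sentences are not narrowed to match. Nor can Tuina's benefit simply be taken as given, since the Abstract says there is little evidence on efficacy and the limitations paragraph calls Tuina experimental.

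**Conclusion.** The point holds as one about analysis and conclusions, of minor to moderate weight. The between-arm comparison validly estimates the effect of adding Yijinjing, as delivered, to Tuina. The within-group tests cannot support a claim that Tuina, or the combination as a whole, is efficacious.

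The size of the error cannot be derived from the document. The 22% to 97% range depends on the assumed non-specific falls and SDs of change. The 3% to 9% for regression to the mean depends on post-treatment figures standing in for the source population and on the assumed correlations. A reader might take the upper figures as the trial's false-positive rate. They are not: they apply to the within-arm tests under assumed natural change and leave the between-arm comparison untouched.

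**What to change.** - **Introduction and Discussion:** restate the hypothesis, and the Discussion sentence on evaluating the efficacy of the protocol, as whether adding Yijinjing to Tuina reduces VAS more than Tuina alone. This point does not require a new choice of primary time point.
- **Specific primary and secondary objectives:** make the between-group comparison the objective and describe within-group change as descriptive. Without this, the objectives would contradict the amended analysis section.
- **Statistical analysis:** replace the paired t tests with within-group mean change and 95% confidence interval. State that efficacy conclusions rest only on the between-arm comparison.

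The cost is wording only: no new patients, data or procedures. The sponsor gives up a broader efficacy statement, which the design could not support in any case.
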